#### SIC scores

Two scores are calculated for each SIC stage. First, the amount of time that a site spends in a stage is calculated by date of entry through date of final activity completed (*i.e*., Duration Score). Because the implementation process is nonlinear, the Duration Score takes into account that activities might not be completed sequentially within a stage. Second, the percentage of activities completed within a stage is calculated (*i.e*., Proportion Score). A site might quickly complete a stage, but not complete all of the activities within that stage. Including both the Duration and Proportion Scores allows for an evaluation of which of these (and the interaction) is most important for successful implementation, and if these findings differ by stage. A third score identifies the final stage achieved (Stage Score).

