#### Predictive ability of scores

Saldana and colleagues [21] found that SIC scores predicted variations in implementation behavior for sites attempting to adopt the MTFC model. Based on stage Proportion and Duration Scores, sites were accurately identified (*i.e*., face validity) through agglomerative hierarchical cluster analyses. Employing Cox proportional hazard models, cluster membership was used to predict successful MTFC start-up. Successful program start-up was predicted by site performance, as measured by the SIC in the first three stages (*i.e*., predictive validity). Sites that completed implementation activities thoroughly (high proportion) but relatively rapidly (duration) were most likely to initiate service; sites that took longer to complete each stage and completed fewer activities had a significantly lower hazard of having their first placement within the study period (HR = 0.190, p = 0.01) than rapid and thorough completers. Implementation condition did not significantly contribute to this model (p = 0.33), suggesting that prediction using the SIC was not attributable to implementation strategy.

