#### Implementation performance: hypothesis testing

Replicating procedures from the original MTFC implementation trial, agglomerative hierarchical clustering methods will be employed to find similarities within sites from each of the EBPs with regard to both Proportion and Duration scores for each stage. Sites will be clustered using each of these variables independently, as well as together. Cox proportional hazard survival models will be conducted with days-to-event as a time to event outcome for each of the three sets of clusters. The events analyzed will include significant milestones such as program start-up and certification. Additional significant events will be determined in collaboration with EBP developers in order to ensure that the SIC is able to accurately predict milestones that are meaningful to the developers. It is hypothesized that each SIC version will produce outcomes similar to those found for MTFC such that both Proportion and Duration are significantly related to successful implementation outcomes [21]. The appropriate rate and necessary proportions might differ between EBPs and service sectors. Universal items will be evaluated to determine if they are more critical than unique items for successful implementation. For any analyses that combine retrospective with the prospective data, this characteristic will be included as a covariate to evaluate any differences.

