### Prediction

The expansion of the SIC will allow for the evaluation of site implementation behavior through observation of progress (both time to completion of key tasks and proportion of tasks completed), thereby providing fine-grained data on progress toward the attainment of key implementation objectives. Such data can serve as ‘milestone implementation outcomes’ in and of themselves. In the proposed study, achievement of these outcomes will be observed within and across the practices being studied. At each stage, data on time to completion and proportion of tasks completed during previous stages can be used to predict future milestone achievement at later stages. This data will be considered in relation to qualitative data collected from end-users to increase understanding of the underlying mechanisms assessed by SIC scores. This type of fine-grained data will allow for an examination of which implementation activities are crucial for program success and which might be encouraged but are not essential.

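### If days-to-event runs from engagement, the Aim 1 Cox models predict a time from its own components, so Duration and combined clusters over-reject; the clock should start at a landmark

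*Protocol article*

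**What the plan says.** The section on implementation performance (Specific aim 1, Analytic plan) groups sites by hierarchical clustering "with regard to both Proportion and Duration scores for each stage". Three groupings result: "Sites will be clustered using each of these variables independently, as well as together". The model is then stated: "Cox proportional hazard survival models will be conducted with days-to-event as a time to event outcome for each of the three sets of clusters". On the outcomes it says: "The events analyzed will include significant milestones such as program start-up and certification". The hypothesis is that "both Proportion and Duration are significantly related to successful implementation outcomes".

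The SIC scores section defines Duration as elapsed calendar time: "the amount of time that a site spends in a stage is calculated by date of entry through date of final activity completed". Proportion is the percentage of a stage's activities that were completed.

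Two other places bear on which stages are used. The account of the earlier MTFC trial, whose procedures are to be replicated, says "Successful program start-up was predicted by site performance, as measured by the SIC in the first three stages". The Prediction subsection of the Discussion says that "data on time to completion and proportion of tasks completed during previous stages can be used to predict future milestone achievement at later stages". Neither place, nor the hypothesis-testing section, gives a time origin for days-to-event, a risk set, or a rule for sites that stop.

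**The concern.** Cluster membership enters the Cox model as though it were known at time zero, but it is built from what happens during follow-up. On a clock that starts at engagement, the pre-implementation Durations make up the first part of days to start-up. A cluster of slow sites must therefore tend to show a longer time to start-up, whether or not slowness predicts anything that happens afterwards.

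This is the stated hypothesis test for the claim that SIC scores predict successful implementation. A significant result could appear when early behaviour carries no information about later success. Repeating the same construction in three more practices could reproduce the same artefact, so agreement with the MTFC results would not validate the measure. The Discussion expects developers to use such findings when they advise struggling sites whether to continue.

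**Working it through.** The article gives no sample size, event count or alpha for the Cox models, and its power paragraph covers only the IRT models. There is no figure to reproduce, so the check is made under a null.

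**Step 1: the overlap.** Let D1, D2 and D3 be the Stage 1–3 Durations and R the remaining time to the milestone. If stages run in sequence and the clock starts at engagement, T = D1 + D2 + D3 + R. Under the null, R is independent of the Durations. Then Cov(D1+D2+D3, T) = Var(D1+D2+D3), which is above zero. As an example, take five independent stages of mean 90 days and coefficient of variation 0.6, with the milestone at the end of Stage 5. The variance per stage is (0.6 × 90)² = 54² = 2,916. Stages 1–3 contribute 3 × 2,916 = 8,748 of a total of 5 × 2,916 = 14,580. The correlation of early Duration with T is √(8,748/14,580) = √0.6 = 0.77, although early pace predicts nothing.

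**Step 2: effect on the test.** Two null simulations were run, both with two Ward clusters and a nominal two-sided 5% test. All settings below are assumptions, except that 15, 35 and 53 sites echo figures in the article (minimum retrospective sites per practice, the preliminary replication, and the earlier trial) and 30 is the 15 retrospective sites plus the possible further 15.

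*Simulation A.* Stage 1–3 Durations are exponential with mean 60 days each, remaining time is independent, no site stops, and censoring is at 900 days. With 35 sites and a mean remaining time of 120 days, Duration clusters reject in 30% of runs, with a median hazard ratio of 0.61 for the slow cluster. Across 20–60 sites and mean remaining times of 60–240 days, rejection is 12–54%. Starting the clock at the end of Stage 3 gives 4–8%, and a median hazard ratio of 1.00 in the 35-site case.

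*Simulation B.* Gamma stage durations as in Step 1, five activities per stage each completed with probability 0.8, follow-up of 1,095 days, 1,000 runs per setting. Random stopping is 0% or 10% per stage. The article expects eight discontinuations a year but gives no denominator, so no rate can be derived from it. Rejection with clusters from Stages 1–3 only and the clock from engagement:

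| Stopped sites | Clusters | n=15 | n=30 | n=35 | n=53 |
|---|---|---|---|---|---|
| None stop | Duration | 28% | 43% | 50% | 59% |
| None stop | Combined | 21% | 31% | 35% | 42% |
| None stop | Proportion | 7% | 7% | 8% | 6% |
| 10% per stage, kept at risk to study end | Duration | 15% | 26% | 29% | 39% |
| 10% per stage, kept at risk to study end | Combined | 35% | 81% | 88% | 98% |
| 10% per stage, kept at risk to study end | Proportion | 33% | 79% | 85% | 97% |
| 10% per stage, censored at stopping | Duration | 36% | 51% | 56% | 69% |
| 10% per stage, censored at stopping | Combined | 20% | 17% | 16% | 15% |
| 10% per stage, censored at stopping | Proportion | 7% | 6% | 8% | 5% |

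**Step 3: the same null with a landmark.** Only sites that finished Stage 3 are kept, the clock restarts there, and clusters use Stages 1–3. Rejection is about 5–10% for all three cluster sets in every setting. The Monte Carlo standard error near 5% is √(0.05 × 0.95/1,000) = 0.7 percentage points. The upper end, at n=15, is therefore a real excess; it fits small, unbalanced clusters.

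**Step 4: what the table separates.** Duration clusters over-reject under every treatment of stopped sites, and so do combined clusters. Stage 1–3 Proportion clusters are near nominal unless stopped sites remain in the risk set.

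**The case against.** Four points on the other side deserve weight.

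*The time origin is not stated.* A condensed article may leave it to a fuller document, and if that document starts the clock after the scored stages, the Duration problem disappears. This stands as a limit on certainty. The predictor, outcome and model are nevertheless fixed in the article, and nothing in it resets the clock.

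*The scores may be confined to earlier stages.* The replication wording and the MTFC account point to Stages 1–3 for start-up, and the Discussion speaks of previous stages. A reader might infer from "with regard to both Proportion and Duration scores for each stage" that all eight stages always enter the clustering. Simulation B, with 10% stopping and stopped sites kept at risk, would then reject in 91–100% of runs for all three cluster sets. The surrounding text makes that reading doubtful, so those figures should not carry the point. The restriction is no cure, however: every row of the table already uses Stages 1–3 only.

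*Low Proportion is not the same as failing to arrive.* A reader might infer that the low-Proportion cluster is simply the failed sites renamed. The SIC scores section does not support this, because it allows a site to finish a stage with activities left undone. The Proportion bias is conditional. It arises when stopped sites stay at risk to study end, or when stages at or after the event or the stopping point enter the clustering. The MTFC account, which speaks of first placement during the study window, hints at the first of these but does not settle it.

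*Stages can overlap.* The article calls the process nonlinear, so days to start-up need not be the exact sum of earlier Durations. This stands. It means the simulated sizes are illustrative, and that completion of Stage 3 could in some sites follow start-up.

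**Conclusion.** The concern holds in a conditional form. If days-to-event runs from engagement or first contact, Stage 1–3 Durations are part of days to start-up, and the Cox test on Duration or combined clusters does not test prediction of later progress. Under the assumptions shown and with no discontinuation, its false-positive rate is about 12–60% at a nominal 5%. With 10% stopping per stage it is 15–69% for Duration clusters, and 15–98% for combined clusters depending on how stopped sites are handled. A landmark brings these to about 4–10%. The direction was the same in every engagement-clock setting; the exact size depends on stage lengths, overlap, number of sites and number of clusters, none of which the article fixes.

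The documents do not support saying that the Proportion analysis is circular in general, that all eight stages are certainly used, or that an engagement clock is stated.

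**What to change.** For each milestone, state a landmark and cluster only on scores accrued before it. For start-up the landmark could be completion of Stage 3 or a fixed number of days after first contact; for certification, a later point chosen on the same principle. Because stages can overlap, keep only sites that are still active and event-free at the landmark. Start time-to-event there. Time-updated scores are an acceptable alternative.

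Treat discontinuation after the landmark as a competing event, and describe sites that stop before it separately, since early failure is of interest in its own right under Aim 2. Keep the engagement-clock, MTFC-style model as a sensitivity analysis for comparison with the earlier work.

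The change is to analysis wording only, because the SIC already records activity completion dates. The costs are that early-stopping sites leave the landmark model, which matters when a practice may contribute as few as 15 retrospective sites, and that the new hazard ratios are not directly comparable with the earlier MTFC figures.

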**Figure 1 F1:**
[figure not shown]
**Conceptual model for implementation research (adapted from Proctor et al. **[3]**) Circled area shows target of proposal.**

The current protocol describes a study in which we seek to narrow this gap by focusing on further development of a measure (*i.e*., the Stages of Implementation Completion; SIC [15]). Through this study, we will examine the generalizability of the SIC across four EBPs in different service sectors serving child and family mental health needs. A glossary of terms is provided in the subsection below.

Glossary of terms used throughout the protocol

**Practice:** A given specific EBP.

**Site:** Newly adopting programs for each EBP.

**Phases:** Pre-Implementation, Implementation, and Sustainability.

**Stages:** The 8 Stages of Implementation on the SIC ranging from Engagement to Competency.

**Universal Items:** Implementation activities identified on the SIC that are common across the EBPs.

**Unique Items:** Implementation activities identified on the EBP-specific SIC that are unique to that EBP.

**Retrospective:** Data from sites that previously adopted the respective EBP prior to project.

**Prospective:** Data from sites that attempt to implement the EBP during the grant period.

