### Retrospective data mapping

#### Mapping

Each of the participating EBPs agreed to provide data related to previous sites that have already implemented the EBP, and this data collection is underway. Research assistants from each of the EBPs were trained by the PI to code retrospective data related to a minimum of 15 formerly implemented sites. This number of sites was selected because it balances time and other resource demands, is sufficient for observing variability in implementation activities, and is sufficient for conducting preliminary Rasch-based measurement models.

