#### Modification

Based on an initial examination of how well activities appear to define the stages, modifications will be made to each version of the SIC as needed. This might include moving activities from one stage to another, deleting activities, or redefining them. This iterative process has occurred for all three of the EBPs, with further modifications expected at the completion of data analyses. If substantive modifications are needed, an additional 15 sites will be coded retrospectively to verify that any modifications improve the measure’s ability to accurately measure implementation. Collaboratively with the developers, a final EBP-specific SIC will be determined for use in prospective data collection.

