#### Prospective data collection

Research staff at the EBP organizations will be trained on data collection procedures for all newly adopting sites. A point person has been identified at each organization to monitor when new sites contact the purveyor to consider implementing the EBP (Stage 1) and to begin tracking activity data on the sites. The purveyors will be trained to note the completion of implementation activities by sites and the resources (both fees and person hours) needed to complete them. Data will include site demographics of all new sites [32]. To ensure reliability of data collected, within each purveyor organization, both the data collection assistant and the EBP site coordinator will independently record 10% of data.

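### As worded, retrospective sites are selected on having implemented the EBP; pooling them with prospective attempters in the start-up Cox models attenuates the cluster effect, and a source covariate does not remove this

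*Protocol article*

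**What the plan says.** The two data sources are defined differently in the glossary of the protocol article. Retrospective is "Data from sites that previously adopted the respective EBP prior to project"; prospective is "Data from sites that attempt to implement the EBP during the grant period". Under Retrospective data mapping (Mapping), the EBPs agreed to "provide data related to previous sites that have already implemented the EBP", and assistants are to "code retrospective data related to a minimum of 15 formerly implemented sites" for each EBP. Under Modification: "If substantive modifications are needed, an additional 15 sites will be coded retrospectively". Under Prospective data collection, a point person at each purveyor picks up new sites at first contact, which is Stage 1 of the SIC.

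Under Implementation performance: hypothesis testing, sites are clustered on Proportion and Duration scores, and the clusters enter Cox models for days to events such as program start-up and certification. Pooled data are handled in one sentence: "For any analyses that combine retrospective with the prospective data, this characteristic will be included as a covariate to evaluate any differences". No other handling of data source is given for these models.

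**The concern.** A site that has already implemented has, on the ordinary meaning of the word, passed start-up. If that is how the retrospective sites were found, attempts that stopped before start-up cannot appear among them, whereas the prospective set includes such attempts.

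The missing failures are not spread evenly. The hypothesis being replicated is that slow, incomplete sites start up less often, so they are the sites most often lost. The slow sites that remain are those that happened to succeed, and they resemble the fast ones. A main-effect covariate for source multiplies the baseline hazard by a constant. It cannot put back the missing slow failures, so the cluster effect within the retrospective set stays distorted and is averaged into the pooled estimate. The source coefficient, which is meant to show whether the two sets differ, would largely measure the sampling rule.

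At stake is the central Aim 1 hypothesis that SIC scores relate to implementation success, and with it the case for early detection of failing sites.

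**Working it through.** The article gives no sample size, event count or power for the Cox models (its Power paragraph covers only the precision of the IRT models), so there is no figure of its own to reproduce. The check is whether the stated handling recovers a known effect.

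**Inputs from the protocol article**
- HR 0.19 for slow, incomplete against rapid, thorough sites (Predictive ability of scores), taken as the true effect.
- At least 15 retrospective sites in each of three EBPs: 3 × 15 = 45.

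**Assumptions not in the article**
- Exponential times to start-up and two clusters of equal size.
- Probability of start-up by end of follow-up in the fast cluster: 0.60, 0.80 or 0.95.
- Retrospective to prospective ratio: 45:45 or 45:90.
- Share of retrospective non-achievers left out: none, half or all.
- No true effect of source.
- 20,000 simulated sites per scenario, to approximate the large-sample value.

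**Why the loss is uneven.** Start-up probability in the slow cluster is 1 − (1 − p)^0.19, where p is the fast-cluster probability. For p = 0.60 this is 1 − 0.40^0.19 = 0.16. Keeping only achievers then drops 40% of fast sites but 84% of slow ones. For p = 0.95 it is 1 − 0.05^0.19 = 0.43, so 5% and 57% are dropped.

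**Results, true HR 0.19 (range over the six scenarios)**

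| Non-achievers left out | Pooled HR, source covariate | Stratified by source | Retrospective only | Source HR (true value 1) |
|---|---|---|---|---|
| None | 0.19 to 0.20 | 0.19 to 0.20 | 0.19 | 0.99 to 1.00 |
| Half | 0.20 to 0.23 | 0.20 to 0.23 | 0.23 to 0.27 | 1.2 to 1.5 |
| All | 0.27 to 0.47 | 0.29 to 0.48 | 0.55 to 0.85 | 1.7 to 5.0 |

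Prospective sites alone gave 0.18 to 0.21 throughout. With a true HR of 0.50 and all non-achievers left out, the pooled HR was 0.64 to 0.72 in the three scenarios run.

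**Closed-form check with explicit discontinuation.** With constant start-up hazard l and discontinuation hazard d, time to start-up among sites that do start up is exponential with rate l + d. The HR among achievers is therefore (l_slow + d_slow)/(l_fast + d_fast). Assume l = 0.5 (slow) and 1.0 (fast) per year, so the true HR is 0.50.
- d = 0.5 (slow) and 0.25 (fast): (0.5 + 0.5)/(1.0 + 0.25) = 0.80.
- d = 1.0 (slow) and 0.25 (fast): (0.5 + 1.0)/(1.0 + 0.25) = 1.20.

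These values describe the retrospective set alone. Simulating the pooled model with a source covariate at ratios of 1:1 and 1:2, with all failures excluded, gave 0.62 to 0.66 in the first case and 0.73 to 0.86 in the second. With half excluded it gave 0.54 to 0.59, and with none excluded about 0.50.

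**The case against.** The strongest reply is that the article does not establish the selection.
- *Implemented* and *adopted* are undefined and used loosely. The preliminary MTFC work describes its 75 retrospective sites as implemented, narrows them to 35 newly adopting sites, and then models their risk of discontinuing. The glossary calls every site newly adopting.
- The abstract describes retrospective data as coming from previous implementation efforts, and says failed as well as successful attempts will be studied.

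This stands as a limit on size: if some failed attempts were coded, the bias shrinks, and with half of them coded it is small. It does not remove the point. The sampling text speaks of sites that already implemented, nothing says that earlier failures are coded, and sites that started up and later discontinued would still be selected on start-up.

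Pooling is also conditional. The sentence applies to any analysis that combines the sets, and prospective-only models are unaffected. That is correct, and the point is limited to pooled models of start-up or earlier events.

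Three stronger readings are tempting but not supported:
- **Reversal.** A reader might infer from the 1.20 above that the pooled effect could change direction. That value is for retrospective sites alone under assumed hazards; no pooled model that was run reversed.
- **Dominance.** A reader might infer that 45 retrospective sites would swamp the prospective ones. Clustering is described within each EBP, so the relevant minimum is 15. No prospective count is given, and the Power paragraph implies that the retrospective set is the smaller.
- **Item difficulties.** A reader might infer that the same selection invalidates the retrospective-prospective comparison under Measurement properties. Rasch models estimate item difficulty separately from site level, so a more successful sample mainly shifts the site measures. An effect on difficulty has not been shown.

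**Conclusion.** The concern holds in a bounded form. If the sampling text means what it says, and start-up models pool the two sources, the cluster effect is biased towards the null and a spurious source effect appears. The stated covariate does not repair this, and nor does stratification by source.

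The range runs from no bias (all initiated attempts eligible) to a pooled HR of 0.27 to 0.47 against a true 0.19 (no non-achievers coded). It rests on exponential times and on the assumed event rates and set sizes; the article does not say where in the range the study lies. The direction is attenuation, so the main risk is that a real predictive value of the SIC is understated, and that a difference between sources is reported which only reflects how sites were chosen.

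**What to change.** 1. State, for each EBP, how the retrospective sites were identified and whether discontinued earlier attempts were eligible. If the sites were drawn regardless of outcome, say so and pool.
2. Otherwise, make the prospective cohort, entered at Stage 1, the primary set for start-up and for any event at or before it. Report pooled start-up results only as a sensitivity analysis.
3. Use retrospective sites for events after start-up, such as certification, with delayed entry at start-up and a source-by-cluster interaction. This is sound only if sites were not also selected on that later event, which item 1 should settle.
4. Do not rely on the interaction to rescue a pooled start-up model. With all non-achievers left out and a shared baseline hazard, the prospective HR read from such a model was 0.17 to 0.18 against a true 0.19. Fit the prospective sites directly.
5. Draw any retrospective sites still to be coded, including the possible additional 15, from all sites that made first contact in a fixed window, whether or not they went on to implement.

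Items 1 to 4 change wording and analysis only. Item 5 will reach few sites, because Trial status reports that MST and MDFT are close to finishing retrospective collection. The real cost is fewer sites, and so less precision, in the primary start-up model.
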